### Inclusion criteria

The inclusion criteria are as follows:

1. subject who is able and willing to give an informed consent is ≥65 years old,

2. is undergoing planned transfemoral TAVI due to severe aortic stenosis, and

3. has calculated eGFR below 60 ml/min/1.73 m2 (using Modification of Diet in Renal Disease (MDRD) formula).

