### Power analysis

The study is powered to detect a 50% reduction in AKI between the groups. The following assumptions and hypotheses correspond to the primary objective:

A = 40% of participants in the sham-controlled group will develop AKI.

B = 20% of participants in the active group will develop AKI.

Hypotheses:

H0: A = B

H1: A ≠ B

Type I error rate = 5% (2-sided) with power = 80%

Drop out/lost to follow –up, rate = 5%

Under the assumption that AKI is relatively common (40%) after TAVI, and that the RenalGuard system has been shown to reduce the incidence of AKI by up to 70% [3,4], we estimated that if there will be a 50% reduction in AKI in the RenalGuard group, the number of patients needed in each group to attain 80% power with an alpha of 0.05, is 92. We plan on recruiting 110 patients in each group (220 total) in order to assure achieving statistical power.

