### Statistical analysis

Standard statistical analyses will be used to compare the aforementioned endpoints in both study arms. We will compare the incidence of AKI and any clinical differences between the groups. Between-group comparisons of clinical endpoints, biomarkers, and imaging data will be performed using the Mann-Whitney U, independent Student’s t tests, or chi square test according to the distribution of variables. All values will be expressed as medians and interquartile ranges for non-normally distributed continuous variables and as mean and standard error for normally distributed variables.

The statistical analysis of the primary endpoint will performed and presented following the intent-to-treat (ITT) principle. A second set of analysis will be performed using a per-protocol population which will include all enrolled patients who completed the procedure and had a 6-month follow-up. Reported *P* values will be two-sided, and *P* <0.05 will be considered as statistically significant. All analyses will be performed using SPSS statistical software.

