## Discussion

The Reduce-AKI trial will investigate whether the use of forced diuresis with matched saline infusion using the RenalGuard system will reduce the occurrence of AKI in patients undergoing elective transfemoral TAVI.

AKI following TAVI is an independent predictor of short- and long-term outcome [6,11] In previously published studies, the incidence of AKI in patients undergoing TAVI ranged from 12% to 41% [6,9-11] with dialysis required in 1.5 to 10% [6,16].

The reasons for the increased risk of AKI in patients undergoing TAVI include elder population with multiple comorbidities, peri-procedural bleedings, hemodynamic instability, distal embolization and the use of nephrotoxic drugs.

Hydration is the cornerstone of AKI prevention. It increases the intravascular blood volume, suppresses the renin-angiotensin-aldosterone system, and promotes dilution and rapid evacuation of contrast media [4,9,17].

Furosemide may reduce the nephrotoxic effect of contrast media, first by increasing the urine flow and thus diluting the contrast media, and second by blocking tubular sodium reabsorption in the loop of Henle, thus reducing tubular workload and concomitant oxygen requirement.

The use of furosemide alone is controversial since it reduces the effective circulating volume and prostaglandin mediated vasodilation, and may lead to dehydration as a result of increased urine output [18,19]. However, when combining hydration with furosemide, studies have shown improved outcomes [3,4].

The RenalGuard system combines all the above methods for prevention of AKI and hydration with forced diuresis with furosemide, while preventing dehydration or fluid overload.

Recently, two randomized controlled trials [3,4] have demonstrated that furosemide-induced diuresis with matched isotonic intravenous hydration using the RenalGuard system reduces AKI in high-risk patients undergoing coronary procedures by up to 71%. In the present study, we chose to evaluate the effect of the RenalGuard system on patients with reduced eGFR since they are at the highest risk for AKI [6,7,20]. In most TAVI patients present with an eGFR below 60 ml/min/1.73 m2, the low eGFR is mostly due to their advanced age (above 80 years). The inclusion/exclusion criteria were very lenient in order to simulate ‘real life’ patients. Therefore, we believe that the Reduce-AKI study will demonstrate a reduction of AKI in this high-risk patient population.

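### The primary AKI comparison is a valid but unadjusted chi-square test; prespecifying baseline eGFR, already known for every patient, would add a small to moderate amount of power at almost no cost

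*Protocol article*

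**What the plan says.** All references are to the protocol article.

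- **Test.** The Statistical analysis section lists Mann-Whitney U, Student's t, "or chi square test according to the distribution of variables". AKI of stage 1 or above is a yes/no outcome, so chi-square is the test that applies. No covariate, regression model or stratified test is named.
- **Covariate.** Under Inclusion criteria, each patient "has calculated eGFR below 60 ml/min/1.73 m2" by the MDRD formula. Under Primary endpoint, serum creatinine is also measured before TAVI. No randomised patient should lack a baseline value.
- **Prognostic role.** The Discussion says the sponsor chose to study the system "on patients with reduced eGFR since they are at the highest risk for AKI".
- **Allocation.** Randomization and blinding describes 1:1 allocation by closed envelopes and states no stratification factor.
- **Design assumptions.** Power analysis gives "A = 40% of participants in the sham-controlled group will develop AKI", "B = 20% of participants in the active group will develop AKI" and "Type I error rate = 5% (2-sided) with power = 80" per cent. From these, "the number of patients needed in each group to attain 80% power with an alpha of 0.05, is 92". Recruitment is set at 110 per group, with 5% loss assumed.

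**The concern.** If a variable measured before treatment predicts the outcome, a prespecified analysis that adjusts for it estimates the treatment effect more precisely from the same patients. Here the variable is collected anyway, the sponsor regards it as prognostic, and the allocation scheme as described does not balance it. The endpoint definition gives a further reason to expect some association below 60. Stage 1 in Table 1 includes an absolute creatinine rise of 0.3 mg/dl. That is 25% of a baseline of 1.2 mg/dl but only 15% of a baseline of 2.0 mg/dl (0.3/1.2 and 0.3/2.0; illustrative baselines).

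What is at stake is some power and precision, not validity. Timing also matters. An eGFR adjustment added after an imbalance has been seen is open to criticism, and one named in advance is not.

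**Working it through.** **1. Inputs.** From Power analysis: p1 = 0.40, p2 = 0.20, two-sided alpha 0.05, power 80%, 110 per group, 5% loss. Evaluable patients per arm: 110 × 0.95 = 104.5, taken as 104.

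**2. The plan's own figure.** With mean rate 0.30, the two-proportion formula without continuity correction gives

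n = [1.96 × √(2 × 0.30 × 0.70) + 0.8416 × √(0.24 + 0.16)]² / 0.20² = (1.2702 + 0.5323)² / 0.04 ≈ 81.2, so 82 per group.

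With the continuity correction, n' = (n/4) × [1 + √(1 + 4/(0.20n))]² ≈ 90.9, so 91. Applying the correction to the rounded 82 gives 91.7, which rounds up to 92. The stated 92 is thus reproduced to within one patient, as a sample size for an unadjusted comparison of two proportions.

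**3. Power of the unadjusted test.** Power = Φ{[0.20 − 1.96 × √(0.42/n)] / √(0.40/n)}. At n = 104: (0.20 − 0.1246)/0.0620 ≈ 1.217, so 88.8%. The same formula gives 84.7% at 92 per arm and 90.5% at 110. With continuity correction the three values, for 92, 104 and 110, are 80.5%, 85.6% and 87.6%. All exceed the 80% target.

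**4. Effect of adjustment, by formula.** If eGFR explains a share R² of the variance in AKI, adjustment acts roughly like enlarging each arm to n/(1 − R²). The documents give no R², so it is an assumption:

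| Assumed R² | 104/(1 − R²) | Power, 40% vs 20% |
|---|---|---|
| 0 | 104.0 | 88.8% |
| 0.02 | 106.1 | 89.4% |
| 0.05 | 109.5 | 90.3% |
| 0.10 | 115.6 | 91.8% |
| 0.15 | 122.4 | 93.2% |
| 0.20 | 130.0 | 94.5% |

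**5. Effect of adjustment, by simulation.** There were 3,000 trials per setting, 104 per arm, with one standard normal covariate and the marginal AKI rates held fixed. The adjusted analysis is a logistic model standardised to a marginal risk difference. R² is that in the control arm.

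| Assumed OR per SD (R²) | 40% vs 20%: chi-square → adjusted | 40% vs 25%: chi-square → adjusted |
|---|---|---|
| 1 (0) | 89.5% → 89.6% | 64.4% → 64.8% |
| 1.5 (0.04) | 89.1% → 90.2% | 63.5% → 65.6% |
| 2 (0.10) | 89.3% → 91.4% | 64.2% → 67.6% |
| 3 (0.19) | 88.1% → 93.1% | 65.9% → 73.0% |

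The simulation error of each power figure is about 0.6 points near 89% and 0.9 points near 65%. The small drift in the chi-square figures down each column is simulation error, because the marginal rates do not change. Each gain compares two analyses of the same simulated trials. Testing the logistic coefficient instead gives 90.0%, 90.9% and 92.7% at OR 1.5, 2 and 3 for 40% versus 20%. With no treatment effect, the adjusted analyses rejected in 4.7% to 5.0% of trials.

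**6. Reading.** At 40% versus 20% the gain is about 1 point at OR 1.5, about 2 at OR 2 and about 4 to 5 at OR 3. If the true difference is 40% versus 25%, it is about 2 to 7 points. With no association there is no gain and no material loss.

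**The case against.** The case for leaving the plan alone is a fair one.

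- **The chi-square test is valid.** It matches the hypothesis under Power analysis, which compares two marginal proportions, and the sample size was built on it. This stands, and it is why the point is not an error.
- **Covariates may be in an analysis plan that is not shown.** This also stands. However, the article does name its tests, and the point is that a better one is available, not that detail is absent.
- **A reader might infer that the protocol names eGFR as the main cause of AKI.** It does not. The Discussion contrasts reduced with preserved kidney function, and its list of reasons for AKI after TAVI leaves eGFR out. Every trial patient is below 60, so the range is cut and no gradient within it is given.
- **A reader might infer that substantial power is being lost.** The documents cannot show that. An odds ratio of 2 or 3 per SD is an assumption, and a weak association would give about 1 point.
- **A reader might infer that a chance eGFR imbalance would bias the unadjusted result.** It would not. The error rate of the chi-square test already allows for such imbalance, and adjustment only reduces the noise it adds.
- **A logistic treatment coefficient is a conditional odds ratio, a different quantity from the difference in proportions that was planned.** This is correct for the raw coefficient. Standardising the fitted risks over all patients returns a marginal risk difference and answers the objection. The form of the eGFR term remains a modelling choice.

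**Conclusion.** The unadjusted chi-square test is valid and has about 89% power at 104 evaluable patients per arm under the sponsor's own 40% versus 20%. No stated target is missed, and the documents support no claim of error or of large lost power.

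The narrower point holds. A baseline variable that the sponsor treats as prognostic, recorded for every patient, goes unused in the primary comparison. Using it would add about 1 to 5 points of power at 40% versus 20% for an assumed odds ratio of 1.5 to 3 per SD, at an unchanged type I error rate. It would cost nothing material if eGFR turned out to be uninformative. The size rests wholly on that assumed association, on a roughly linear effect of eGFR on the log-odds scale, and on 104 evaluable patients per arm. It is a worthwhile, low-cost improvement.

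**What to change.** Before unblinding, and preferably before the efficacy interim analysis planned at 50% enrolment, prespecify the following for the primary intention-to-treat analysis:

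- a logistic regression of AKI on treatment arm with baseline eGFR as a continuous covariate, using the value obtained before randomisation;
- the standardised (marginal) risk difference from that model with a 95% CI as the reported effect, so that it answers the hypothesis stated under Power analysis;
- the form of the eGFR term, for example linear, fixed in advance;
- the chi-square test retained as a supportive analysis.

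The sample size need not change. The article reports 41 of 220 patients recruited, so at publication there was time to make the change. The cost is a sentence or two in the plan, one extra model with a standardisation step, and a modelling assumption for the eGFR term. No new data are needed.

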### Transcatheter aortic valve implantation procedures

All patients will undergo transfemoral aortic valve implantation per standard clinical practice. Briefly, the femoral artery will be accessed with the standard endovascular technique, thereafter the procedure involves advancing a large catheter (18 Fr) through the aortic arch, retrogradely crossing the aortic valve, following by balloon valvuloplasty and stent-valve implantation. During the procedure, the patients will receive analgesics and anxiolytics as per protocol.

Post-procedural pharmacotherapy, sheath removal, and deployment of hemostatic devices will be left to the discretion of the attending cardiologists. Following treatment in the catheterization laboratory, medical treatment throughout hospitalization and follow-up treatment will be left to the discretion of the treating physician managing patient care on the hospital wards. Specific agents added or withdrawn will be made by treating physicians and will not be influenced by the study team.

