**Figure 3 F3:**
[figure not shown]
Treatment algorithms of the sham-controlled/passive RenalGuard group (group A) and the active RenalGuard group (group B).

Before the procedure: A standard 18 to 22 gauge catheter will be inserted into a peripheral vein of the arm and a standard Foley catheter will be placed in the bladder for urine collection (as performed routinely for all TAVI procedures). The intravenous (IV) line and the urinary catheter will be connected to the RenalGuard System. The RenalGuard System will be set to 0% match; that is, the urine rate and volume will be measured, but it will not deliver matched IV normal saline. The system will be computed to deliver continues IV normal saline at a rate of 100 cc/h (100 cc/h is the routine average fluid infusion rate in TAVI procedure) during the procedure and up to 6 h after the procedure. Neither a routine IV bolus of saline nor a routine IV furosemide will be given before the procedure.

During the procedure: The urine and infusion volumes will be measured by the RenalGuard system throughout the catheterization procedure and for 6 h after the last contrast dose. Additional IV fluids can be added as needed according to the clinical decision of the anesthesiologist or the attending physician.

We will analyze the quantity and quality of urine during the duration of the procedure.

**Group 2** - Active Group (Figure 3B). Treatment as group 1 and in addition, the RenalGuard system will be activated (active mode).

Before the procedure: A standard 18 to 22 gauge catheter will be inserted into a peripheral vein of the arm and a standard Foley catheter will be placed in the bladder for urine collection (as performed routinely for all TAVI procedures). The IV line and the urinary catheter will be connected to the RenalGuard System. The RenalGuard System will be set to 100% match; that is, the urine rate and volume will be measured and the system will deliver volume of IV normal saline that is matched to the volume of urine produced by the patient. An initial IV bolus (250 ml) of normal saline over 30 min will be administered approximately 90 min before the procedure; in patients with heart failure, the volume of the bolus can be reduced to 150 ml. Furosemide will then be administered as a single intravenous bolus of 0.25 to 0.5 mg/kg at the physician’s discretion. When a urine output rate >300 ml/h will be achieved, the patients will be sent to the catheterization laboratory.

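### The per-protocol set is defined without reference to the assigned treatment, so it cannot show the effect of the strategy as delivered

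*Protocol article*

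**What the plan says.** In the protocol article, Statistical analysis, the primary endpoint analysis is to be "performed and presented following the intent-to-treat (ITT) principle". A second analysis uses a "per-protocol population which will include all enrolled patients who completed the procedure and had a 6-month follow-up". These are the only two conditions.

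The section on transcatheter aortic valve implantation procedures shows what the procedure is: "the procedure involves advancing a large catheter (18 Fr) through the aortic arch". The word is used in this sense throughout the article. It does not refer to the RenalGuard treatment.

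The Study protocol section sets out the assigned treatments in detail. For the active arm, "The RenalGuard System will be set to 100% match", a saline bolus is given, and "Furosemide will then be administered as a single intravenous bolus of 0.25 to 0.5 mg/kg". Matching then runs through the catheterization and for six hours after the final contrast dose. There is also a release rule: "When a urine output rate >300 ml/h will be achieved, the patients will be sent to the catheterization laboratory". For the sham arm the console is set to 0% match, and "Neither a routine IV bolus of saline nor a routine IV furosemide will be given before the procedure". Additional IV fluids are allowed on clinical grounds in both arms. Once the patient leaves the catheterization laboratory, other medication is left to the ward: "Specific agents added or withdrawn will be made by treating physicians and will not be influenced by the study team".

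**The concern.** A per-protocol analysis is there to show what happens among patients who received the strategy they were allocated. Here the article specifies the strategy closely and then uses none of it to decide membership. An active patient whose console stayed passive, or who received no bolus or furosemide, counts as per-protocol active. A sham patient run in active mode counts as per-protocol sham.

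If the intention-to-treat result were null, a reader would turn to this second analysis to ask whether the strategy failed or was not delivered. As defined, it cannot answer. Close agreement between the two analyses would also say nothing about delivery, because delivery does not separate them.

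**Working it through.** **1. The rule against the assigned treatment.**

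| Element of the assigned strategy (Study protocol) | In the per-protocol rule? |
|---|---|
| Active: 100% match | No |
| Active: saline bolus | No |
| Active: furosemide bolus | No |
| Active: matching until 6 h after contrast | No |
| Sham: 0% match | No |
| Valve implantation completed (both arms) | Yes |
| 6-month follow-up (both arms) | Yes |

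The set differs from intention to treat only by dropping patients without a completed implantation or without 6-month follow-up. Departures from the assigned treatment are not removed.

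**2. The plan's own figure.** Inputs from Power analysis: 40% AKI in sham, 20% in active, two-sided 5%, 80% power, 92 per group.

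- Pooled-variance formula: n = [1.96·√(2·0.30·0.70) + 0.84·√(0.40·0.60 + 0.20·0.80)]² / 0.20² = 81.2, so 82.
- With continuity correction: (81.2/4)·[1 + √(1 + 4/(81.2·0.20))]² = 90.9, so 91.

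The stated 92 is reproduced to within one patient. This point does not depend on it, but the 40% and 20% rates are used below.

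**3. Illustration of dilution.** The documents give no rate of non-delivery, so the fraction p is assumed. It is also assumed that an untreated active patient has the sham risk, and that p is the same among patients who meet the two membership conditions as among all patients.

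Active rate = 0.20·(1 − p) + 0.40·p; difference = 0.40 − active rate.

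| p | Active rate | Difference | Risk ratio | Power, 104 per group |
|---|---|---|---|---|
| 0% | 20% | 20 points | 0.50 | 0.89 |
| 10% | 22% | 18 points | 0.55 | 0.81 |
| 20% | 24% | 16 points | 0.60 | 0.70 |
| 30% | 26% | 14 points | 0.65 | 0.58 |

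The 104 per group is 110 × 0.95 = 104.5, rounded down (planned recruitment less the stated 5% dropout). Power = Φ{[d·√n − 1.96·√(2·m·(1 − m))] / √(a·(1 − a) + 0.40·0.60)}, where a is the active rate, d the difference and m the mean of the two rates.

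The same rows apply to both analysis sets, because the per-protocol rule takes out none of the untreated patients. A set restricted to delivered treatment would, under these assumptions, sit on the first row.

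**The case against.** **The stakes are low.** Intention to treat is primary, the test is for two-sided superiority, and no decision rule rests on the second analysis. This stands in full. A reader might infer that the trial's main conclusion is at risk; it is not.

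**Deviation criteria usually sit in an analysis plan that is not shown.** That would excuse silence. Here the article states a rule that takes in all patients meeting two conditions, so a later document would have to correct it.

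**Departures may be rare.** The active arm has a urine-output release rule, furosemide is repeated when output falls, and the centre already uses the console routinely. A reader might infer that departures are likely, but no passage gives a rate or supports that word. The release rule is only a partial safeguard, because it checks urine output and not whether matching is running.

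**Low eGFR does not strengthen the point.** A patient with poor renal function who received bolus, furosemide and matching but responded weakly was still treated as assigned. Response is not delivery.

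**Permitted care is not a departure.** Extra fluids are allowed in both arms. The sham text rules out only routine furosemide before the procedure, so clinically indicated use is not prohibited. The freedom given to ward physicians overlaps with study treatment only in the hours after the catheterization.

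**Sham furosemide cannot be assumed to dilute.** A reader might subtract a further 2 points for 10% of sham patients receiving it (0.9 × 40% + 0.1 × 20% = 38%). That gives them the full active-arm benefit. The Discussion calls furosemide without matched hydration controversial and a possible cause of dehydration, so even the sign of the effect is not established.

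**A stricter set brings its own bias.** Excluding sham patients for any furosemide, or active patients whose matching was stopped for clinical reasons, selects on the course after randomization. Low urine output is itself an AKI criterion in Table 1. This stands and limits the fix.

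**Conclusion.** The point holds for the definition. The per-protocol set depends on completing the implantation and the 6-month follow-up and on nothing about the assigned treatment. Patients with the wrong console mode, or active patients without the bolus and furosemide, therefore stay in it, and it cannot show the effect of the strategy as delivered.

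The consequence is confined to the supportive analysis. Its size is unknown. The fall from 20 to 18, 16 or 14 points is conditional on assumed non-delivery of 10%, 20% or 30% in the active arm and on untreated patients having the 40% sham risk. If every patient received the allocated strategy, nothing would be diluted. The documents do not support a claim that departures are frequent, nor a figure for sham furosemide.

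**What to change.** Before unblinding, define per-protocol membership by the allocated strategy having been started:

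- **Active:** console at 100% match, with the protocol bolus and furosemide given.
- **Sham:** console at 0% match, not run in active mode.

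Do not select on urine output: only the active arm has the target, and response reflects kidney function. Do not select on permitted extra fluids, clinically indicated furosemide, or stopping early for clinical reasons. Report each of these by arm, together with the percentage who received the assigned strategy. Examine sham furosemide and early stopping only in a sensitivity analysis labelled as such. The 6-month condition is a separate question, but the same sentence can be revised for both.

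This changes analysis wording and not patient care. The console already measures urine and infusion volumes. The article reports 41 of 220 patients recruited and blinded biostatisticians, so at that stage the rule could still be fixed in advance. The costs are a slightly smaller set and a check of console and furosemide records. Some post-randomization selection remains even under this definition, so the analysis should stay supportive of intention to treat.

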## Abstract

**Background:**

Acute kidney injury (AKI) is observed in up to 41% of patients undergoing transcatheter aortic valve implantation (TAVI) and is associated with increased risk for mortality. The aim of the present study is to evaluate whether furosemide-induced diuresis with matched isotonic intravenous hydration using the RenalGuard system reduces AKI in patients undergoing TAVI.

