## Background

Acute kidney injury (AKI) is a frequent complication of coronary angiography, and is associated with unfavorable outcomes including major cardiovascular events, renal replacement therapy, prolonged hospitalization, and early death [1,2]. Recently, two randomized controlled trials have demonstrated that furosemide-induced diuresis with matched isotonic intravenous hydration using the RenalGuard system (PLC Medical Systems, Milford, Massachusetts, USA) [3,4] reduces AKI in high-risk patients undergoing coronary procedures.

Elderly patients undergoing TAVI have a high prevalence of chronic kidney disease (CKD) and therefore are at increased risk to develop AKI (Table 1). In recent reports, AKI has been observed in up to 41% of patients undergoing TAVI [5-11] and was associated with a four times higher post-procedural mortality [11-14]. ‘RenalGuard’ is a Conformité Européenne (CE)-approved system that is being used worldwide. The objective of this randomized sham-controlled study is to assess the beneficial effect of treating TAVI patients with this system in reducing the occurrence of AKI.

**Table 1 T1:** **Definition of acute kidney injury post transcatheter aortic valve implantation (TAVI) according to the VARC-2 classification **[15]**]**

**Stage 1**	Increase in serum creatinine to 150 to 199% of baseline
	**OR**
	Increase of ≥0.3 mg/dl (26.4 mmol/L)
	**OR**
	Urine output <0.5 ml/kg/h for >6 but <12 h
**Stage 2**	Increase in serum creatinine to 200 to 299% of baseline
	**OR**
	Urine output <0.5 ml/kg/h for >2 but <24 h
**Stage 3**	Increase in serum creatinine to ≥300% of baseline
	**OR**
	Increase of serum creatinine of ≥4 mg/dL (354 mmol/L) with an acute increase of at least 0.5 mg/dl (44 mmol/l)
	**OR**
	Urine output <0.3 ml/kg/h for >24 h
	**OR**
	Anuria for >12 h

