### Primary endpoint

The primary endpoint is reduction of acute kidney injury (stage 1 or above) at 48 to 72 h. Serum creatinine level will be measured prior to TAVI and at 48 to 72 h post-procedure. AKI will be defined as stage 1, 2 or 3 according to VARC-2 AKI classification [15] (Table 1).

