### Secondary endpoints

The secondary endpoints are to assess whether the RenalGuard system can reduce major adverse clinical events (MACE) defined as a composite of all-cause mortality, myocardial infarction, AKI, 30 day readmission rate, and dialysis. Another secondary endpoint is to assess whether the RenalGuard system can lower 30-day readmission rate and 30-day congestive heart failure exacerbation rate.

Other secondary objectives are to determine whether endothelial function assessment can predict AKI using the EndoPat™ system, to determine whether chronic statins treatment offers any clinical benefit in preventing contrast induced nephropathy, to determine if carotid Doppler analysis can predict AKI occurrence and to determine the predictive value of different biomarkers in assessing the clinical outcome in TAVI patients.

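### The per-protocol set for a 48 to 72 h endpoint is conditioned on a 6-month follow-up, so this secondary analysis can select on a consequence of AKI

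*Protocol article*

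**What the plan says.** The Primary endpoint section sets an early outcome: "The primary endpoint is reduction of acute kidney injury (stage 1 or above) at 48 to 72 h". The Statistical analysis section places the primary endpoint analysis on a set "following the intent-to-treat (ITT) principle" and then adds a second set of analyses on a "per-protocol population which will include all enrolled patients who completed the procedure and had a 6-month follow-up".

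The article links AKI to later death in three places. The Abstract says that AKI "is associated with increased risk for mortality". The Background section says that it "was associated with a four times higher post-procedural mortality". The Discussion states: "AKI following TAVI is an independent predictor of short- and long-term outcome".

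The article gives no reason for tying a 48 to 72 h outcome to a 6-month contact, and no rule on how a death before 6 months is classified. Table 2 lists physical examination, blood tests and cardiac echo at 6 months. The Adverse events section says that events at follow-up are found by interview and from medical records.

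**The concern.** Membership of the second set is settled up to six months after the outcome is known. On the plain reading, patients who die in between have no 6-month follow-up and leave the set, although their AKI status was observed. By the protocol's own account, deaths are more frequent among AKI patients, so AKI cases are removed more often than the rest. Patients lost after discharge also leave, although their primary outcome is complete.

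At stake is a second AKI comparison printed beside the ITT result. It would understate AKI in both arms. If death after AKI is more or less common in one arm, it could also distort the difference between arms, and excess deaths in an arm would lower that arm's apparent AKI rate.

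**Working it through.** **The plan's own figure.** The Power analysis section gives 92 per group for 40% vs 20%, two-sided alpha 5%, power 80%.
- Pooled two-proportion formula: [1.960·√(2·0.3·0.7) + 0.842·√(0.4·0.6 + 0.2·0.8)]² / 0.2² = 81.2, so 82.
- With continuity correction: (81.2/4)·[1 + √(1 + 4/(81.2·0.2))]² = 91.0, so 91. Starting from the rounded 82 gives 91.7, so 92.

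The stated figure reproduces. With the planned 110 per group, power is 90.5% (pooled formula, no continuity correction).

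**Inputs.**
- AKI risk p: 0.40 sham ("A = 40% of participants in the sham-controlled group will develop AKI") and 0.20 active, from the Power analysis section.
- Mortality ratio, AKI to no AKI: 4, from the Background section. That sentence gives no time frame, so using the ratio at 6 months is an assumption.
- 6-month mortality without AKI, m0: not in the article. Assumed 2%, 5% and 10%. With AKI, m1 = 4·m0.

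**Formula.** The AKI rate left in an arm after deaths are removed is p′ = p(1 − m1) / [p(1 − m1) + (1 − p)(1 − m0)].

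Example with m0 = 5%, m1 = 20%:
- Sham: 0.40·0.80 / (0.32 + 0.60·0.95) = 0.32/0.89 = 36.0%.
- Active: 0.20·0.80 / (0.16 + 0.80·0.95) = 0.16/0.92 = 17.4%.
- Removed: 110·(1 − 0.89) = 12.1 sham patients, of whom 44·0.20 = 8.8 had AKI; 110·(1 − 0.92) = 8.8 active patients, of whom 22·0.20 = 4.4 had AKI.

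| m0 / m1 | Sham vs active AKI | Difference (points) | Risk ratio | Odds ratio | Removed of 110 (sham, active) | Power |
|---|---|---|---|---|---|---|
| no 6-month condition | 40.0% vs 20.0% | 20.0 | 0.50 | 0.375 | 0, 0 | 90.5% |
| 2% / 8% | 38.5% vs 19.0% | 19.5 | 0.49 | 0.375 | 4.8, 3.5 | 88.5% |
| 5% / 20% | 36.0% vs 17.4% | 18.6 | 0.48 | 0.375 | 12.1, 8.8 | 84.7% |
| 10% / 40% | 30.8% vs 14.3% | 16.5 | 0.46 | 0.375 | 24.2, 17.6 | 75.5% |

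**When the null is preserved.** The odds in the reduced set are p/(1 − p) · (1 − m1)/(1 − m0). If m1 and m0 are the same in both arms, the second factor cancels between arms. The odds ratio is then unchanged, and equal AKI risks stay equal.

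**When it is not.** Let mortality after AKI differ by arm, with no true effect on AKI and m0 = 5%. All mortality figures here are illustrative.
- AKI 40% in both arms; mortality after AKI 20% sham, 10% active: 36.0% vs 0.36/0.93 = 38.7%, a false disadvantage of about 3 points.
- AKI 40% in both arms; 20% sham, 30% active: 36.0% vs 0.28/0.85 = 32.9%, a false benefit of about 3 points.
- AKI 30% in both arms; 20% sham, 40% active: 0.24/0.905 = 26.5% vs 0.18/0.845 = 21.3%, a false benefit of 5.2 points. With 110·0.905 = 99.6 and 110·0.845 = 93.0 patients, the standard error is √(0.265·0.735/99.6 + 0.213·0.787/93.0) = 6.1 points.

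**The case against.** The strongest reply is that little depends on this set. The primary endpoint is analysed by ITT, and the article gives the per-protocol set no co-primary or confirmatory role. That stands, and it limits the severity.

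Second, the article does not say that deaths are excluded. Since follow-up events are also found in medical records, a documented death could be counted as completed follow-up. Then only losses would leave: at the 5% stated in the Power analysis section, 110·0.05 = 5.5 patients per arm. This reading is possible but less natural, and even then patients with a known primary outcome would be dropped without a stated reason.

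Third, the size rests on assumed mortality. The 10%/40% row implies 0.4·40% + 0.6·10% = 22% mortality in the sham arm, which nothing in the article supports. The 5.2-point example doubles mortality after AKI in the active arm, to eight times the non-AKI rate, and is still below one standard error. These are fair limits. The Safety section does name fluid overload as the main safety issue, so a difference in mortality by arm cannot be ruled out, but no figure is given.

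A reader might go further and infer three things that the article does not support:
- That MACE, a "composite of all-cause mortality, myocardial infarction, AKI, 30 day readmission rate, and dialysis", becomes a survivors-only analysis. The article does not say that the second set is used for MACE or mortality.
- That adherence to the assigned RenalGuard mode is ignored. Detailed adherence criteria may sit in the full protocol or analysis plan, which are not shown.
- That the rule necessarily produces a false benefit. If death depends on AKI alone it cannot, and otherwise the direction is open.

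**Conclusion.** The definition is wrong as written: it conditions an outcome fixed by 72 h on a contact at 6 months that the outcome itself can prevent. Severity is moderate, because only the secondary analysis is touched and the ITT conclusion stands.

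On the plain reading that early deaths leave the set, with assumed mortality of 2% to 10% without AKI and the fourfold ratio carried to 6 months, the AKI difference shrinks from 20.0 to between 19.5 and 16.5 points. The risk ratio moves slightly away from 1. A spurious or masked effect additionally requires mortality after AKI to differ by arm.

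**What to change.** For the 48 to 72 h endpoint, delete the 6-month condition. Define the per-protocol set by facts fixed by 72 h: procedure completed, assigned RenalGuard mode delivered, and AKI status assessable. If the set is also to be used for MACE or mortality, state that deaths before 6 months stay in and count as events.

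The cost is about one sentence in the protocol or analysis plan. It needs no new data, since the procedure, device and creatinine records are already part of the trial. The Trial status section reports 41 of the planned 220 patients recruited, so the change can be made and dated well before unblinding.
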